### Sample size and power

There will be three study arms in the proposed study; (1) intervention, (2) set menu control, and (3) control. Due to the potential similarity in each arm, a cluster-random trial will be considered, which takes into account between-cluster variation [94]. Relevant intervention literature shows effect sizes varying from 30-80 % [26, 29, 31, 39, 42, 45, 46, 49–51], which will be adequate for the proposed sample size design. The study will evaluate the difference in disease indices, quality of life and perceived and biological indicators of stress between the intervention and control groups, as well as within each group according to individual levels of intervention participation. Therefore, estimated sample sizes are displayed in Table 1 under a variety of effect sizes and drop-out levels in order to obtain a 0.95 significance level and 0.8 power of study. Our target recruitment level will be 150 participants according to an 80 % power level, in an effort to capture smaller effect sizes. This will correspond to an approximate 45 % response rate (*N* = 336), which is well within response and participation in other studies among the MUSC lupus cohort. Based on these results there is good to adequate power for most analyses to make the proposed project feasible.

**Table 1 Tab1:** Estimated sample size calculations

Estimated sample sizes				
Effect size	0.4	0.6	0.7	0.8
Sample size per arm (No drop out)	51	23	18	14
Sample size per arm (10 % drop out)	86	38	28	22
Sample size per arm (15 % drop out)	91	41	30	23

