### Data analytic plan

#### Quantitative data analysis

Data will be entered immediately after specified collection points into an Excel worksheet that will be built upon after each collection point and imported into SAS for data manipulation. To minimize risks to confidentiality, all data will be de-identified by assigning a numeric code to each participant and labeling all materials corresponding to that participant with their unique identifier. Additionally, data files that include personal identifiers will be stored separately from signed consent forms in locked file cabinets that only the Principal Investigator will have access to. The basic experimental design and corresponding data analyses will represent a one-between subjects (intervention versus control and intervention versus set menu control) and one-within or repeated factor (pre, post, and follow up assessments) crossed factorial design, with multiple dependent outcome measures (disease activity and damage, perceived and biological indicators of stress, quality of life, and urine catecholamines). The multivariate (multiple qualitatively distinct measures at multiple times) approaches to repeated measures [95, 96], based on the general linear model or general linear mixed model, will be used to test for pre-post-follow up changes between the intervention group and the control groups, as well as for exploratory correlations with urine catecholamines. These approaches provide better description of longitudinal patterns for each dependent variable and they are easier to successfully implement and generally more powerful than the use of covariant models when multiple outcome measures are considered simultaneously [96]. *P* < 0.05 will be used to indicate statistical significance. The data from all randomized participants will be analyzed. Multiple imputations will be used to estimate missing data from dropouts and those participants who do not complete follow up evaluations. We will evaluate the first 12 months to address primary outcomes and exploratory analyses will be conducted after 12 months once participants are given the option to cross over. Basic descriptive statistics such as means, ranges, and standard deviations will be calculated and tabulated for quantitative data using SAS (SAS Institute, Cary, North Carolina). Project-specific frequencies and percentages will be presented as a recruitment diagram according to CONSORT guidelines.

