### Qualitative data analysis

Qualitative data will be analyzed using QSR NVivo 8 (Qualitative Solutions and Research, Pty Ltd, Victoria, Australia), a software program for managing, coding, analyzing, and retrieving qualitative data. Data will be coded electronically in NVivo 8 and printed out by code, reviewed for accuracy, and examined for links to other codes. This “axial coding” [95] process will connect code categories and identify relationships between codes which are suggestive of themes. Furthermore, as part of the ongoing analytic process, comparing and contrasting themes within and across the two strata (“constant comparison method”) will detect similarities and differences in the data [95]. Verbatim quotes will be selected to validate researchers’ coding and interpretations. The Z test and Student’s *t* test will be used for continuous variables satisfying normality assumption, and Mann Whitney *U* test and Kruskal-Wallis Test will be applied for variables which cannot satisfy the normal assumption. All statistical comparison tests will be at a 95 % significance level.

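### The significance level is given as 0.95 (sample size) and 95 % (comparison tests) where the type I error rate of 0.05 belongs; Table 1 does not show which test or sidedness was used

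*Protocol article*

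**What the plan says.** Three statements in the protocol article bear on the significance level.

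- Sample size and power: Table 1 is presented "in order to obtain a 0.95 significance level and 0.8 power of study".
- Quantitative data analysis: P "< 0.05 will be used to indicate statistical significance".
- Qualitative data analysis, closing a list of Z, t, Mann-Whitney and Kruskal-Wallis tests: "All statistical comparison tests will be at a 95 % significance level".

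The sample size section also says: "Our target recruitment level will be 150 participants according to an 80 % power level". None of these sections says that 0.95 or 95 % is meant as a confidence level. None says whether the tests are one-sided or two-sided, or which test Table 1 assumes.

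**The concern.** A significance level is the probability of rejecting a true null hypothesis. The values 0.95 and 95 % are one minus that probability. So two operative statements, the premise of the sample size and a rule for comparison tests, disagree with the P < 0.05 rule printed between them.

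What is at stake is traceability. The sentence that should fix the alpha input of Table 1 gives a value that cannot be right. A reader would normally repair such a slip by assuming 0.05 and checking it against the table, but here the check does not give one answer.

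**Working it through.** **Inputs.** Table 1 gives effect sizes 0.4, 0.6, 0.7 and 0.8, taken here as standardized differences (SD = 1), which is an assumption. Power is 0.80, so z = 0.8416. The printed sizes per arm are 51/23/18/14 with no drop-out, 86/38/28/22 with 10 % and 91/41/30/23 with 15 %. Sidedness and test are not stated, so several were tried.

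**Step 1: is the stated pair possible?** An unbiased test has power of at least its own level. At level 0.95, power is therefore at least 0.95, and a plan for 0.8 cannot exist.

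**Step 2: does alpha = 0.95 reproduce Table 1?** For two groups, n per arm = 2(z_alpha + z_power)² / d².

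- Two-sided 0.95: z_alpha = 0.0627, the sum is 0.9043, and 2 × 0.9043² = 1.636. Dividing by d² gives 10.2/4.5/3.3/2.6, rounded up to 11/5/4/3.
- One-sided 0.95: z_alpha = -1.6449, the sum is -0.8032, and the formula has no meaning.

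No cell of Table 1 is reproduced.

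**Step 3: does 0.05 reproduce it?**

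| Calculation, 80 % power | 0.4 | 0.6 | 0.7 | 0.8 |
|---|---|---|---|---|
| Printed, no drop-out | 51 | 23 | 18 | 14 |
| Two groups, two-sided 0.05, normal formula | 98.1 | 43.6 | 32.0 | 24.5 |
| One-sample or paired t, two-sided 0.05 | 51.01 | 23.79 | 18.03 | 14.30 |
| Printed, 10 % drop-out | 86 | 38 | 28 | 22 |
| Two groups, one-sided 0.05, normal formula, divided by 0.90 | 85.9 | 38.2 | 28.0 | 21.5 |
| Two groups, one-sided 0.05, t-test, divided by 0.90 | 86.63 | 38.94 | 28.82 | 22.26 |
| Printed, 15 % drop-out | 91 | 41 | 30 | 23 |
| Two groups, one-sided 0.05, normal formula, divided by 0.85 | 90.9 | 40.4 | 29.7 | 22.7 |
| Two groups, one-sided 0.05, t-test, divided by 0.85 | 91.73 | 41.23 | 30.52 | 23.57 |

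The one-sided t-test sizes before drop-out are 77.97/35.04/25.94/20.03. If decimals are cut off, the paired t row gives the no-drop-out row exactly, and the one-sided two-group t rows give all eight drop-out cells exactly. The normal formula agrees with the drop-out rows to within one patient. One-sided 0.05 is numerically the same as two-sided 0.10 here, so Table 1 cannot tell these two apart.

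**Step 4: can one calculation give all three rows?** No, and this does not depend on alpha. Allowing for 10 % drop-out takes 51 to 51/0.9 = 56.7, not 86. Worked backwards, 86 × 0.9 = 77.4 and 91 × 0.85 = 77.4, so the two drop-out rows share a base of about 77 for effect size 0.4, while the no-drop-out row shows 51.

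**The case against.** The strongest reply is that this is a slip of terminology. If 0.95 and 95 % are read as confidence levels, all three statements describe one threshold, and P < 0.05 is stated correctly in the section that governs the between-arm analyses. Because the pair 0.95 and 0.8 is impossible, no statistician could apply it as written. The 95 % sentence also closes the qualitative analysis section, so it is unclear whether its word for all tests reaches the repeated-measures models. Nearly all of this stands. It limits the size of the point, but it does not make the two sentences correct.

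A reader might go further and infer that Table 1 was calculated at alpha 0.95, or that the trial would call almost any difference significant. The document does not support either reading: alpha 0.95 reproduces no cell, and the quantitative section gives a usable rule.

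A reader might also want to repair the sample size sentence by writing two-sided 0.05. The document does not support that either. It states no sidedness, and two-sided 0.05 between groups gives about 98/44/32/25 before drop-out, which is not what Table 1 prints.

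**Conclusion.** The point holds as a labelling error in two operative sentences. The confidence level stands where the type I error rate of 0.05 belongs, in conflict with the article's own P < 0.05. Changing the label alters no number in Table 1 and no planned analysis.

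The change of label alone is not enough, because the table fits two different premises: a two-sided 0.05 one-sample or paired test for the row without drop-out, and a one-sided 0.05 between-group test for the rows with drop-out. These matches rest on reading the effect sizes as standardized differences and on common t-test or normal formulas. They show what fits the printed figures, and the authors must confirm what was actually done. Whether 50 per arm gives enough power is a separate question that does not follow from the mislabelled level.

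**What to change.** 1. In the sample size section, replace 0.95 with a significance level of 0.05. In the qualitative analysis section, replace 95 % with 5 %. Both then agree with P < 0.05.
2. State the sidedness of the tests, and name the test and sidedness that produced each row of Table 1.
3. If the between-arm tests are two-sided, restate Table 1 on that basis. With the normal formula at two-sided 0.05 and 80 % power, the rows become 99/44/33/25 with no drop-out, 110/49/37/28 with 10 % (divide by 0.90, round up) and 117/52/39/30 with 15 % (divide by 0.85, round up). If the between-arm tests are one-sided, say so in all three sections and derive the no-drop-out row from the same between-group test as the other two.

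The cost is two corrected sentences, one added statement and, if needed, a recalculated table. Trial conduct is not affected.

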### Randomization

Within a month of all signed informed consent forms and baseline assessments being returned, the Biostatistician or their graduate assistant (GA) will enter baseline data and randomly assign each participant to one of three study arms: (1) intervention, (2) set menu control, or (3) control, returning that information to the principal investigator (PI) and Intervention Coordinator. Randomization will be stratified according to level of education (i.e., high school diploma or greater vs no diploma), or employment (more than 30 h per week vs less than 30 h), or income (SSI vs ≤ 25,000 vs > 25,000), depending on the completeness of data provided by the MUSC Study Coordinator. Within a month of randomization, the Intervention Coordinator will contact 50 intervention arm participants and assess and record their intervention modes of choice. The intervention coordinator will provide URL for listserv, support group details, and coordinate mailing of arthritis kits as applicable. The Intervention Coordinator will then link interested intervention arm and all set menu control arm participants to CDSMP’s in their area. The GA will make courtesy calls to the 50 participants in the control group letting them know of their designation and when they can expect contact and next round of evaluation materials to be completed and returned for compensation.

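### Table 1's drop-out rows cannot be derived from its no-drop-out row, and only the no-drop-out row supports 50 patients per arm at an effect size of 0.4

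*Protocol article*

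**What the plan says.** The section Sample size and power presents Table 1 "in order to obtain a 0.95 significance level and 0.8 power of study". The table gives the number per arm for four effect sizes:

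| Effect size | 0.4 | 0.6 | 0.7 | 0.8 |
|---|---|---|---|---|
| No drop-out | 51 | 23 | 18 | 14 |
| 10% drop-out | 86 | 38 | 28 | 22 |
| 15% drop-out | 91 | 41 | 30 | 23 |

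The section cites effect sizes of 30–80% from the literature and goes on: "Our target recruitment level will be 150 participants". That number is tied to 80% power and to the wish to detect smaller effects. The closing statement is "Based on these results there is good to adequate power for most analyses to make the proposed project feasible". No test, sidedness or within-patient correlation is named.

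The Quantitative data analysis section describes the comparison as "one-between subjects (intervention versus control and intervention versus set menu control", crossed with repeated assessments, and says that P "< 0.05 will be used to indicate statistical significance". The Qualitative data analysis section adds: "All statistical comparison tests will be at a 95 % significance level".

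Sample size and power also says "Due to the potential similarity in each arm, a cluster-random trial will be considered, which takes into account between-cluster variation", whereas the Randomization section has the biostatistician or assistant "randomly assign each participant to one of three study arms".

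**The concern.** An allowance for drop-out multiplies a sample size by a known factor. The step from the first row of Table 1 to the other two is far larger than 10% or 15% drop-out can explain, so the rows must come from different calculations.

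This matters because of where the target sits. Fifty per arm is almost exactly the 51 in the no-drop-out row at 0.4, the smallest effect tabulated. If that cell is on a different basis from the rest, the link between 150 patients, 80% power and smaller effects is lost. A reader of the results would then credit the trial with more ability to exclude a moderate effect than the article has shown.

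**Working it through.** **Inputs.** Table 1 as above. Power 0.80. Alpha 0.05, reading the 0.95 significance level as 1 − alpha, in line with the P-value threshold in the analysis section. 50 per arm, from Study design. Two assumptions are mine: effect sizes are standardised mean differences, and tests are two-sided unless marked otherwise, because the article does not say.

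**1. Do the rows agree?** This step needs no assumption about the test. With n/(1 − drop-out):

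- From 51: 51/0.90 = 56.7 and 51/0.85 = 60.0. The table prints 86 and 91.
- Expected ratios to the first row are 1.11 and 1.18. The table's ratios are 1.56–1.69 for 10% and 1.64–1.78 for 15%.
- Back from the drop-out rows at 0.4: 86 × 0.90 = 77.4 and 91 × 0.85 = 77.4. At 0.6: 34.2 and 34.9. At 0.7: 25.2 and 25.5. At 0.8: 19.8 and 19.6.

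The two drop-out rows agree with each other, on a base of about 77, 34–35, 25 and 20. The first row (51, 23, 18, 14) has a different base.

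**2. Which calculations reproduce the table?** No single formula tried gives all three rows.

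| Calculation, 80% power | 0.4 | 0.6 | 0.7 | 0.8 |
|---|---|---|---|---|
| Paired t, two-sided | 51.01 | 23.79 | 18.03 | 14.30 |
| Two-sample t, two-sided, residual variance halved | 50.03 | 22.80 | 17.03 | 13.30 |
| Two-sample t, one-sided | 77.97 | 35.04 | 25.94 | 20.03 |
| the same /0.90 | 86.63 | 38.94 | 28.82 | 22.26 |
| the same /0.85 | 91.73 | 41.23 | 30.52 | 23.57 |
| Two-sample t, two-sided | 99.08 | 44.59 | 33.02 | 25.52 |

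The first row matches the paired test rounded down. It also matches a between-arm test with halved variance, rounded up. The drop-out rows match the one-sided two-sample test rounded down.

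**3. What does 50 per arm give?** Two-sample t-test, two-sided 0.05, one unadjusted comparison, no credit for repeated measures:

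| Effect size | 50 per arm | 45 (10% drop-out) | 42.5 (15% drop-out) |
|---|---|---|---|
| 0.3 | 32% | 29% | 28% |
| 0.4 | 51% | 47% | 45% |
| 0.5 | 70% | 65% | 63% |
| 0.6 | 84% | 80% | 78% |
| 0.7 | 93% | 91% | 89% |
| 0.8 | 98% | 96% | 95% |

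The smallest effect with 80% power is 0.57, 0.60 and 0.61 respectively. A one-sided test at 0.4 with 50 per arm has 63%.

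**4. What would repeated measures have to supply?** For 80% at 0.4 with 50 per arm, the residual variance must fall to 50/98.11 = 0.51 of its unadjusted value, where 98.11 is the two-sided normal-approximation sample size.

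- One follow-up adjusted for baseline: factor 1 − ρ², so ρ is about 0.70 (about 0.75 after 15% drop-out).
- Mean of two follow-ups adjusted for baseline, equal correlations: factor (1 + ρ)/2 − ρ². At ρ = 0.5 this is 0.75 − 0.25 = 0.50, giving 80% with no drop-out, 76% after 10% and 73% after 15%. At ρ = 0.6 it is 0.44, giving 85%, 81% and 79% (78.5% before rounding).

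**The case against.** The best defence is that 51% is not the power of the planned analysis. The article plans a repeated-measures model and judges primary outcomes over the first 12 months, which contain assessments at baseline, 6 and 12 months. With two baseline-adjusted follow-ups, a correlation of 0.5 would give 80% at 0.4 before drop-out, and the first row of Table 1 fits just such a halved variance. This stands. A reader might infer that the true power at 0.4 is 51%, or that the first row is certainly a within-group test. The article supports neither, because it names no test and no correlation. The same silence means that it cannot be relied on for 80% either, and no choice of correlation reconciles the rows with one another.

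A second defence is that the closing sentence speaks only of most analyses and the text attaches no number to smaller effects. This stands in part. For 0.6 and above the sentence is fair: 84% or more with full follow-up and 78% or more after 15% drop-out, even without repeated measures. A reader might infer that the sentence is false as a whole; it is not. What lacks support is the claim about smaller effects, since 0.4 is the smallest effect tabulated.

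On clustering, a reader might infer that the article claims to have allowed for it in the figures. It says only that a cluster-random design would be considered. That is a wording conflict with individual randomisation and is secondary here.

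**Conclusion.** Table 1 is internally inconsistent. This follows from its own figures, whatever test was used. At 0.4, the 50 per arm chosen is supported only by the no-drop-out row. The drop-out rows ask for 86–91 per arm, which is 258–273 patients over three arms.

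The size of the shortfall depends on the analysis assumed. Without credit for repeated measures and two-sided at 0.05, power at 0.4 is about 51%, falling to about 45–47% after 10–15% drop-out. The trial then has 80% power for a difference of about 0.57, or 0.60–0.61 after drop-out. Reaching 80% at 0.4 requires a correlation that the article does not state: about 0.5 with two baseline-adjusted follow-ups or about 0.7 with one, both before drop-out. The names of the tests behind the rows are inferred from the numerical match.

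**What to change.** Recompute all of Table 1 by one method and state it. With a two-sided 0.05 two-sample t-test, 80% power and n/(1 − drop-out), the numbers per arm are:

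| Effect size | 0.4 | 0.6 | 0.7 | 0.8 |
|---|---|---|---|---|
| No drop-out | 100 | 45 | 34 | 26 |
| 10% drop-out | 111 | 50 | 37 | 29 |
| 15% drop-out | 117 | 53 | 39 | 31 |

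If repeated measures are to be credited, apply the same method with the assumed correlation, the number of follow-ups and the form of adjustment written out.

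State that 150 patients give about 80% power for a standardised difference of about 0.6 in each pairwise contrast, without credit for repeated measures. Remove the clause that ties the target to smaller effects, or qualify it with the correlation it needs. Express the significance level as 0.05 and give the sidedness. Separately, reconcile the sentence about a cluster-random trial with the individual allocation in the Randomization section.

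The cost is a correction to one table and a few sentences. Trial status reports 153 patients already randomised, and the change calls for no more. The stated power becomes less favourable.

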### Data analytic plan

#### Quantitative data analysis

Data will be entered immediately after specified collection points into an Excel worksheet that will be built upon after each collection point and imported into SAS for data manipulation. To minimize risks to confidentiality, all data will be de-identified by assigning a numeric code to each participant and labeling all materials corresponding to that participant with their unique identifier. Additionally, data files that include personal identifiers will be stored separately from signed consent forms in locked file cabinets that only the Principal Investigator will have access to. The basic experimental design and corresponding data analyses will represent a one-between subjects (intervention versus control and intervention versus set menu control) and one-within or repeated factor (pre, post, and follow up assessments) crossed factorial design, with multiple dependent outcome measures (disease activity and damage, perceived and biological indicators of stress, quality of life, and urine catecholamines). The multivariate (multiple qualitatively distinct measures at multiple times) approaches to repeated measures [95, 96], based on the general linear model or general linear mixed model, will be used to test for pre-post-follow up changes between the intervention group and the control groups, as well as for exploratory correlations with urine catecholamines. These approaches provide better description of longitudinal patterns for each dependent variable and they are easier to successfully implement and generally more powerful than the use of covariant models when multiple outcome measures are considered simultaneously [96]. *P* < 0.05 will be used to indicate statistical significance. The data from all randomized participants will be analyzed. Multiple imputations will be used to estimate missing data from dropouts and those participants who do not complete follow up evaluations. We will evaluate the first 12 months to address primary outcomes and exploratory analyses will be conducted after 12 months once participants are given the option to cross over. Basic descriptive statistics such as means, ranges, and standard deviations will be calculated and tabulated for quantitative data using SAS (SAS Institute, Cary, North Carolina). Project-specific frequencies and percentages will be presented as a recruitment diagram according to CONSORT guidelines.

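### The planned comparison of change from baseline, with no baseline adjustment stated, gives up precision at the smaller effects the trial wants to detect

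*Protocol article*

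**What the plan says.** Under Quantitative data analysis, the article sets one between-subjects factor (arm) and "one-within or repeated factor (pre, post, and follow up assessments) crossed factorial design". Baseline is therefore an outcome at the first level of the time factor. The approach is multivariate repeated measures "based on the general linear model or general linear mixed model", and these models "will be used to test for pre-post-follow up changes between the intervention group and the control groups". No baseline covariate is mentioned, and no constraint that the arms share a baseline mean. The approach is preferred partly because it is "generally more powerful than the use of covariant models when multiple outcome measures are considered simultaneously". Primary outcomes are judged over the first 12 months, and missing data are to be multiply imputed.

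Under Randomization, arms are assigned after the baseline assessments are returned. "Randomization will be stratified according to level of education", or employment, or income, "depending on the completeness of data provided by the MUSC Study Coordinator". The analysis section neither includes nor excludes a stratum term.

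Under Sample size and power, 150 participants (50 per arm) are chosen so that smaller effects can be detected. The cited literature is said to show effects of 30 to 80%.

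**The concern.** Because baseline is measured before randomisation, the arms have equal baseline means in expectation. A crossed arm-by-time model that estimates a separate baseline mean in each arm discards that knowledge. Its contrast at a later visit subtracts the whole baseline value, noise included, where a regression would subtract only the part that predicts follow-up. The cost is precision, not bias.

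The cost matters because the trial aims at smaller effects with 50 per arm, and those are the effects for which it has least power. Adding patients is not an easy remedy: recruitment draws on 336 database patients, and Trial status reports 153 already randomised. Every mailed outcome has a scheduled baseline value, so the information needed is already being collected. The sentence on power could also be read as a reason against baseline adjustment and carried into the final analysis.

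**Working it through.** **Inputs from the article.** 50 per arm; power 0.80; P "< 0.05 will be used to indicate statistical significance", with sidedness not stated (two-sided is used here); Table 1 effects of 0.4, 0.6, 0.7 and 0.8, read as standardised differences. The sample size section's "in order to obtain a 0.95 significance level and 0.8 power of study" is read as alpha 0.05.

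**Assumed.** Outcome SD 1 at each visit, and r from 0.3 to 0.8, because the article gives no correlation.

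**The plan's own figures.** Table 1's dropout rows follow from a one-sided two-sample formula, n = 2(1.645 + 0.842)²/d², divided by (1 − dropout). For 10% dropout this gives 85.9, 38.2, 28.0 and 21.5, against 86, 38, 28 and 22 printed. For 15% it gives 90.9, 40.4, 29.7 and 22.7, against 91, 41, 30 and 23. The no-dropout row (51, 23, 18, 14) does not fit a two-arm comparison: two-sided gives 99, 44, 33 and 25, and one-sided gives 78, 35, 26 and 20. It does fit a two-sided paired formula, which gives 51.0, 23.7, 17.9 and 14.2. So 50 per arm meets Table 1 with dropout at 0.6 and above, but not at 0.4 (86 to 91).

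**Per-participant variances, single outcome, complete data.**
- Difference in change from baseline to 12 months: 2(1 − r)
- Baseline as covariate: 1 − r² = (1 − r)(1 + r)
- Ratio, adjusted to change: (1 + r)/2, below 1 for every r below 1

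**Power** = Φ(d / √(2v/50) − 1.96), where v is the variance above. **Detectable effect at 80% power** = 2.80 × √(2v/50).

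| r | v, change | v, adjusted | Variance saved | Power at 0.4 | Detectable effect (SD) | n per arm for 0.4 |
|---|---|---|---|---|---|---|
| 0.3 | 1.40 | 0.91 | 35% | 39.4% → 55.4% | 0.66 → 0.53 | 138 → 90 |
| 0.5 | 1.00 | 0.75 | 25% | 51.6% → 63.7% | 0.56 → 0.49 | 99 → 74 |
| 0.7 | 0.60 | 0.51 | 15% | 73.3% → 80.0% | 0.43 → 0.40 | 59 → 51 |
| 0.8 | 0.40 | 0.36 | 10% | 88.5% → 91.5% | 0.35 → 0.34 | 40 → 36 |

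Simulation with 50 per arm and an effect of 0.4 agrees: 39%, 51% and 73% for change, and 53%, 63% and 79% adjusted, at r of 0.3, 0.5 and 0.7. With 15% dropout (42.5 per arm on average), power at 0.4 goes from 34% to 49%, 45% to 57%, 66% to 73% and 83% to 87% for the four values of r.

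**At an effect of 0.6**, the same formula gives 72% → 88% at r = 0.3, 85% → 93% at r = 0.5 and 97% → 99% at r = 0.7. Only a low r leaves the planned analysis short there.

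**Stratum.** If the stratification factor explained a further 2 to 10% of residual variance (assumed), adjusted power at 0.4 and r = 0.5 would rise from 64% to 65–68%.

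**The case against.** Four objections deserve an answer.

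**The repeated-measures format is not at fault.** This stands. The plan allows a mixed model, and one that keeps baseline as an outcome with a common mean across arms recovers essentially the same precision as a covariate. But the text describes a plain crossed design and tests differences in change, and its natural reading leaves baseline means free. This is a stated choice of contrast, not a detail left open.

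**The remark on power is qualified.** It concerns several outcomes considered together, does not define covariant models, and rests on a reference not available here. A reader might infer that the article flatly claims change analysis beats baseline adjustment, and so has the comparison backwards. The wording does not support that. What can be said is narrower: for any one outcome the remark is no reason to forgo baseline adjustment, which is equally available when there are several outcomes.

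**The stratum.** A reader might infer that the plan leaves the stratification factor out of the model. It is silent, and an article commonly leaves such terms to a fuller document. The gain is small in any case.

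**The trial is not simply under-powered.** This also stands. A flat figure of about 51% power at 0.4 corresponds to a change analysis only at r = 0.5; across assumed r of 0.3 to 0.8 it runs from 39% to 88.5%. Within the article's own effect range, 0.6 and above is adequately covered unless r is low.

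**Conclusion.** The point holds as one of efficiency. As described, the 12-month comparison for a single outcome is a change-score contrast: unbiased under randomisation, but less precise than a baseline-adjusted one for every r below 1. The variance saving from adjustment is 35% at r = 0.3 and falls to 10% at r = 0.8. In power at 0.4 SD, that is a gain of about 16 points at the low end and 3 at the high end. The benefit matters mainly for the smaller effects the trial says it wants to detect.

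This rests on an assumed r, equal SDs across visits, complete (or imputed) data, two-sided 0.05 and analysis in the arm assigned by randomisation. The rule under Safety monitoring that recodes non-participants as controls would break the last of these; it is a separate matter.

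**What to change.** - For each mailed outcome, model the 6- and 12-month values in a linear mixed model with arm, visit, arm-by-visit and the baseline value of that outcome. Alternatively, keep baseline as an outcome with one mean common to all arms. Name the adjusted 12-month difference as the between-arm contrast.
- Put the same terms in the multiple-imputation model.
- As a minor addition, include the stratification factor actually used, and state which of the three it was.
- Handle urinary catecholamines separately. They are collected only at baseline and 24 months, in a sub-sample of 50, so a 6- and 12-month model cannot cover them. Adjust the 24-month value for its baseline.
- Limit the sentence on covariant models so that it cannot be used as a reason against baseline adjustment.

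The cost is wording and programming, with no new data. Since 153 participants are randomised and 30 have completed all assessments, record the change as a dated amendment before any unblinded analysis.
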